### Study design, participants, and procedure

2.1

This study is an addition to the NCT05186337 clinical trial. We will conduct a prospective longitudinal observational MRI study. We will invite older adult patients diagnosed with BD type I or II who are about to receive FROA-BD at the Bipolar and Depressive Disorder Unit at the Hospital Clinic of Barcelona to participate. The sample will comprise at least 32 patients (50% males and 50% females). Inclusion criteria will include: (a) aged 60 or over; (b) diagnosis of BD type I or type II according to the Diagnostic and Statistical Manual of Mental Disorders (DSM-5) (35); (c) full or partial remission at the time of assessment, defined as scores ≤14 on the Hamilton Assessment of Depression Scale (HDRS) (36, 37) and ≤ 10 on the Young Mania Rating Scale (YMRS) (38, 39); (d) presence of functional impairment defined as a total score ≥ 11 on the FAST (40); and (e) written informed consent to participate in the study. Exclusion criteria will include: (a) estimated intelligence quotient (IQ) lower than 85; (b) having received a structured psychological intervention within the last 6 months; (c) presenting any central nervous system condition, other than mental disorders, that may affect neuropsychological performance or any physical condition that may hamper participation or assimilation of the contents of the intervention (e.g., severe visual or hearing impairment); (d) presence of any current comorbid psychiatric condition; (e) history of cranioencephalic trauma; and (f) having received electroconvulsive therapy 6 months before the inclusion study.

After consenting, participants will undergo a demographic, clinical, functional, and neuropsychological assessment and an MRI session. Afterward, patients will receive the 32 sessions of FROA-BD throughout 4 months while continuing their usual pharmacological treatment. Finally, after finishing the FROA-BD, patients will undergo a second clinical, functional, and neuropsychological assessment and a second MRI session. For more details on the FROA-BD protocol and program description, see Montejo et al. (20).

Discontinuation criteria will include (a) withdrawal of consent by the participant; (b) significant clinical relapse or hospitalization for any episode; and (c) not attending more than eight sessions during the intervention.

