### Data analysis

2.7

The primary outcome will be the correlation between pre-post changes in the activation of the dorsolateral and dorsomedial prefrontal cortex during the working memory n-back task (2-back vs. baseline) and pre-post changes in psychosocial functioning assessed with the Functioning Assessment Short Test (FAST) (63). Specifically, we will conduct three correlations: one for the left dorsolateral, one for the bilateral dorsomedial, and one for the right dorsolateral prefrontal cortex. We will use a permutation test to correct for multiple testing (three correlation tests).

For the secondary analyses, we will conduct two kinds of correlations: (a) pre-post changes in MRI data with pre-post changes in cognition and psychosocial functioning outcomes, and (b) baseline MRI data with pre-post changes in cognition and psychosocial functioning outcomes. We will include as covariates the variables from age, sex, bipolar disorder type, medication (use of lithium, antiepileptics, antidepressants, and antipsychotics), illness history (duration of the illness and number of episodes), or educational level that show statistically significant associations with the MRI signal or the cognition/functioning outcome; in case that several variables show statistically significant associations, we will select those still showing statistical significance in multiple regression. We will report results for structural MRI analyses using both familywise error rate (FWER) < 0.05 based on conservative permutation tests (64) and threshold-free cluster enhancement (TFCE) (65) and uncorrected *p* < 0.001 (at the exploratory level). For spectroscopy, we will use linear models. Finally, for fMRI analyses, a paired t-test will be conducted on single-subject contrast to examine temporal changes in activation, employing the Nilearn toolbox. We will break down and localize clusters using SDM ‘imgcalc’ tool (66).

We will also repeat all the analyses on those results that reach statistical significance according to sex to explore potential differences.

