Despite the FROA-BD neural substrates not being studied yet, our research team has already analyzed the neural markers that predict the efficacy of other psychotherapies. For instance, the frontal areas activation involved in salience and interoception processing, including the dorsomedial prefrontal cortex, predicted improvement with cognitive-behavioral psychotherapy in anxiety-related disorders (67). Miskowiak et al. (31) found that pre-treatment dorsolateral prefrontal hypoactivation predicted greater improvement in executive function after 10 weeks of action-based cognitive remediation in patients with BD. They also found an early dorsolateral prefrontal activity change during the working memory task that predicted improved executive functions after treatment completion (29). The same research group investigated not only associations between pre-treatment functional brain activation and response to treatment of cognitive remediation, but also explored the association between pre-treatment structural brain measures and treatment success. Specifically, they found that a minor baseline dorsolateral prefrontal cortical thickness was associated with greater treatment efficacy on executive functions, contrary to what they expected (30). In addition, vertex-based analysis also revealed an association between smaller superior temporal gyrus volume at pre-treatment and improved executive function after receiving cognitive remediation.

Concerning verbal learning and memory, the neural correlates of treatment-related improvements remain unclear, with a dearth of studies and conflicting findings (30, 68, 69). In this sense, some studies used a picture encoding task, an fMRI paradigm that probes visual memory for investigating the neural correlates of verbal memory improvement. Another study conducted in BD and major depressive disorder, after 10 weeks of cognitive remediation demonstrated an increase in the activation in lateral and medial prefrontal, superior temporal and lateral parietal regions in the n-back tasks and an activation increased in the bilateral hippocampus during the memory task (28). In our protocol, we will use a verbal memory encoding fMRI paradigm based on the RAVLT, with verbal material (auditory), which could be a highly sensitive verbal learning paradigm and more able to elicit hippocampal activation (70).

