In addition, exploring the potential differences in treatment response or neural correlates based on sex could be valuable. For that reason, we will carry out exploratory analyses separately. We will repeat all the analyses on those results that reach statistical significance according to sex to explore potential differences depending on sex. To date, there is limited evidence suggesting a gender effect on memory-related functional activation (71–73) and the research examining sexual differences in the neural substrates of recall memory is inconclusive (74, 75). Regarding the efficacy of cognitive remediation in mood disorders no clear effect of sex has been found in treatment response (76). Some clinical manifestations are different between sexes in OABD, where females scored higher on anxiety and hypochondriasis, and had a higher number of hospitalizations. In contrast, males had more lifetime substance abuse disorders (77) suggesting the existence of different clinical and disease underlying mechanisms between the two sexes. Other potential confounding variables, in addition to age and sex, that will be considered in the analysis, could be pharmacological treatment, illness history, and educational attainment due to the association with cognitive performance, response to treatment, and brain functionality.

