This project has potential limitations. First, we expect a loss of participants during the intervention or the follow-up period, mainly due to the higher frequency of different medical comorbidities usually presented by this group of patients. Although Nuclear Magnetic Resonance is a safe procedure that does not involve radiation emission, it may lead to a loss of subjects in the study due to contraindications such as patients with a pacemaker or any metal prosthesis, panic attacks and agoraphobia or claustrophobia. Nevertheless, we expect a reduced number of dropouts given that most of the patients will be followed in our unit. The possibility of participant attrition has also been considered in the sample size calculation. Besides, other approaches have been considered to address this risk, such as expanding the participants’ recruitment to other local mental health centers. Lastly, including not only patients in full, but also in partial remission, with a more representative real-world population in the daily clinical practice, will also contribute to limiting this potential issue (78). We acknowledge that a RCT design would also provide information about the differences in brain changes between the individuals following the FROA-BD program and those in a control group. However, in this study, we were not interested in the differences in brain changes between the FROA-BD and a control group but in the brain changes associated with a higher efficacy among individuals following the FROA-BD program. Another potential limitation of the study is the lack of resting state fMRI. However, we included MRI sequences based on previous works about cognitive remediation in BD.

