This project aims, for the first time, to contribute knowledge on the neural underpinnings of functional remediation for OABD, to optimize this psychotherapy. Consequently, the project’s outcomes will establish the knowledge for enhancing functional remediation, potentially benefiting this group of patients. The findings are expected to directly improve psychosocial functioning and quality of life for this population. As emphasized by the International Society for Bipolar Disorders (ISBD) (5, 78), assessing the impact of novel treatments on the brain, such as through MRI, can provide knowledge in identifying specific changes in function and structure associated with cognitive performance and, in turn, may then offer insights into the potential effectiveness of the treatment. In fact, the use of neuroimaging could yield several additional benefits. On the one hand, it could provide information on how cognitive rehabilitation modulates different brain functions, offering insights into optimizing this psychotherapy. On the other hand, baseline MRI could serve to predict, for each individual, the extent of improvement in cognition and functioning in cognitive remediation. Identifying key targets associated with improved treatment response, on one side, and the neural correlates underlying cognitive function, on the other side, contributes to designing strategies aimed at precision and personalized medicine. This approach can help provide specific tools to patients, ensuring a tailored benefit based on their individual characteristics.

In conclusion, this study aims to investigate the neural mechanisms underlying FROA-BD, a specific intervention designed to improve functional and cognitive outcomes in older adults with BD. We will use different structural and functional magnetic resonance imaging to provide insight into its neural mechanisms. We consider the results of this study can provide a basis for developing personalized treatments in the elderly population and contribute to optimizing the design of the therapy itself.

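### Objective (b) relates baseline MRI to raw change without the baseline value of the outcome, so it cannot show that MRI predicts improvement beyond the score already in hand

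*Protocol article*

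**What the plan says.** The Objectives and Data analysis sections define two kinds of secondary correlation. The second is "b) baseline MRI data with pre-post changes in cognition and psychosocial functioning outcomes". The outcome is therefore the raw difference between the two assessments; no model of the post-treatment score and no residualised change is described.

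The covariates come from a stated pool: "We will include as covariates the variables from age, sex, bipolar disorder type, medication (use of lithium, antiepileptics, antidepressants, and antipsychotics", followed by "illness history (duration of the illness and number of episodes), or educational level that show statistically significant associations with the MRI signal" or with the outcome. Each variable enters only if it is statistically significant. The Discussion names largely the same confounders again: beyond age and sex, those "that will be considered in the analysis, could be pharmacological treatment, illness history, and educational attainment". Neither list contains the baseline FAST score or the baseline value of the cognitive outcome.

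The Discussion gives the intended use: "baseline MRI could serve to predict, for each individual, the extent of improvement in cognition and functioning".

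**The concern.** A change score contains the baseline score with a minus sign. If a patient was in a poor state on the day of the baseline assessment, part of the later improvement is a return to that patient's usual level. An MRI measure that shares this transient component will go with larger improvement even if it carries no information about response to the programme.

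The second issue does not depend on any bias. A clinician who wants to know who will improve already has the baseline score. For MRI to be useful as a predictor it must add to that score, and a correlation with raw change that leaves the score out does not test this. At stake is whether a positive result for objective (b) can be read as prediction or only as a restatement of baseline severity. There is no comparison group to help separate the two; the Discussion says that "we were not interested in the differences in brain changes between the FROA-BD and a control group".

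**Working it through.** **The article's own figure.** The article gives no numerical result for objective (b). The only computable figure is the power of the primary analysis: about 80% for r = 0.56 with 28 patients and three tests. With two-sided alpha 0.05/3 (sidedness and alpha are assumed), simulation of the Pearson test gives 0.79 and the Fisher z approximation 0.78. The statement reproduces. It is used here only to fix n = 28.

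**Inputs.** From the article: n = 28, the raw-change outcome, the covariate pool, and the uncorrected p < 0.001 threshold for structural maps. Assumed, because the article does not give them: rho (correlation of the marker M with the observed baseline score Y0) of 0.3 to 0.5, r (correlation of Y0 with the post score Y1) of 0.5 to 0.8, and equal SDs, set to 1.

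**Case A: M follows the observed baseline and adds nothing about Y1 given Y0.**

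- corr(M, Y1) = rho*r, so cov(M, Y1 - Y0) = rho*r - rho = -rho(1 - r).
- SD(Y1 - Y0) = sqrt(2(1 - r)).
- corr(M, Y1 - Y0) = -rho(1 - r)/sqrt(2(1 - r)) = -rho*sqrt((1 - r)/2).

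Each cell gives this correlation and, in brackets, the simulated rejection rate at nominal 5% two-sided, n = 28:

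| | rho 0.3 | rho 0.4 | rho 0.5 |
|---|---|---|---|
| r = 0.5 | -0.15 (11%) | -0.20 (18%) | -0.25 (26%) |
| r = 0.7 | -0.12 (9%) | -0.15 (12%) | -0.19 (17%) |
| r = 0.8 | -0.09 (8%) | -0.13 (10%) | -0.16 (13%) |

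A second simulation with more runs agrees to within about one point (12% and 25% for rho 0.3 and 0.5 at r = 0.5; 9% and 17% at r = 0.7). With Y0 in the model, rejection is about 5% throughout. At nominal 0.001, with rho = 0.5 and r = 0.7, raw change rejects in 1.0% of runs and the adjusted model in 0.1%.

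**Case B: M follows only stable true severity, measurement error is independent of M, and true severity does not change.**

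- corr(M, Y0) = corr(M, Y1) = rho, so cov(M, Y1 - Y0) = 0. Raw change is unbiased, and simulated rejection is about 5%.
- The adjusted model is now the one that departs from zero: partial r = rho(1 - r)/sqrt((1 - rho^2)(1 - r^2)).
- rho = 0.3, r = 0.8: 0.06/sqrt(0.91 x 0.36) = 0.10.
- rho = 0.5, r = 0.5: 0.25/sqrt(0.75 x 0.75) = 0.33.
- Simulated rejection for the adjusted model over this grid is 8% to 41%. M helps here only by removing noise from the baseline score; it says nothing about response.

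The two cases are mirror images. The article gives no means of telling which applies to a given MRI measure.

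**The case against.** The strongest reply is that raw change is not wrong in general. Baseline error biases the correlation only if the marker is correlated with that error. Volume, thickness, surface area and diffusion measures are plausibly stable traits, which puts them nearer case B; task activation may share state with the baseline score. Without randomisation, the choice between change score and baseline adjustment rests on an assumption that the data cannot settle. This stands, and it is why adjustment should be added to the raw-change analysis and not replace it. It does not answer the second issue: a claim of prediction beyond the baseline score needs a model that contains that score.

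The 8% to 26% is also at nominal 5%, whereas the structural maps use familywise control or p < 0.001. That stands for absolute size. Familywise control does not remove the bias, because in case A the association with change exists at the voxel.

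A reader might infer three stronger points that the article does not support.

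- *Entry selection makes it worse.* Entry requires "presence of functional impairment defined as a total score ≥ 11 on the FAST". In case B, truncation on the observed score pushes the raw-change correlation in the opposite direction to case A (0.11 to 0.22 in simulations with illustrative cut-offs), and adjustment does not cure it. The criterion also concerns FAST, not the cognitive outcomes.
- *The earlier results have the sign of this artefact.* The Discussion reports that "pre-treatment dorsolateral prefrontal hypoactivation predicted greater improvement in executive function", and a similar finding for thinner cortex. But the Hypotheses section tentatively expects thicker frontal and parietal cortex to predict improvement, and the Introduction links greater left dorsomedial prefrontal thickness to impairment. The article does not establish that thinner cortex goes with a worse baseline score.
- *The regional tests are affected.* The three prefrontal regions belong to the primary change-with-change test. Objective (b) is whole-brain analysis and spectroscopy.

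**Conclusion.** The point holds in a limited form. The article states both the outcome (raw change) and the covariate pool for objective (b), and the baseline value of the outcome is in neither, so this is not simply detail left to another document. Followed as written, the plan cannot show prediction beyond the baseline score.

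The bias is conditional. It is about -0.10 to -0.25 in correlation if the marker shares the transient part of the baseline score, and zero, before entry selection, if it follows only stable severity. These sizes rest on assumed rho and r. A reader might infer that the planned correlation is invalid and should be replaced by the adjusted model; case B shows why that does not follow.

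Severity is minor: the objective is labelled secondary and exploratory, the primary test is untouched, and the Discussion speaks of what baseline MRI could do, not of a result.

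**What to change.** For objective (b), in both the whole-brain maps and the spectroscopy linear models, add a model of the post-treatment outcome on baseline MRI with the baseline value of the same outcome as a fixed covariate, kept whether or not it is significant. Report it beside the raw-change correlation.

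State that baseline MRI predicts improvement beyond the baseline score only where the adjusted coefficient supports it, and say where the two analyses disagree. A disagreement should be read with both cases above in mind: shared transient state on one side, noise in the baseline score on the other.

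The cost is a sentence or two in the analysis section. No new data are needed, since any outcome analysed as pre-post change already has a baseline value. The adjusted model spends one degree of freedom and has a somewhat wider standard error where MRI and the baseline score are strongly correlated.

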**Methods:**

Thirty-two individuals with OABD in full or partial remission will undergo a magnetic resonance imaging (MRI) session before receiving FR-OABD. After completing the FR-OABD intervention, they will undergo another MRI session. The MRI sessions will include structural, diffusion-weighted imaging (DWI), functional MRI (fMRI) with working memory (n-back) and verbal learning tasks, and frontal spectroscopy. We will correlate the pre-post change in dorsolateral and dorsomedial prefrontal cortices activation during the n-back task with the change in psychosocial functioning [measured with the Functioning Assessment Short Test (FAST)]. We will also conduct exploratory whole-brain correlation analyses between baseline or pre-post changes in MRI data and other clinical and cognitive outcomes to provide more insights into the mechanisms and explore potential brain markers that may predict a better treatment response. We will also conduct separate analyses by sex.

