### Hypotheses

1.1

The main hypothesis of this study is that, after completing the FROA-BD program, patients will show a correlation between the changes in their dorsolateral or dorsomedial prefrontal cortex activation during a working memory task (compared to baseline) and improved psychosocial functioning.

The secondary, explorative hypotheses are that there exist correlations between changes in other MRI-derived brain signals and cognition and psychosocial improvements and between baseline MRI-derived brain signals and cognition and psychosocial improvements. Based on the above studies finding neural correlates of cognition remediation in BD, we hypothesize that the correlations will involve structural MRI and task-based fMRI. However, due to the study’s novelty, we do not have clear hypotheses about their specific brain locations. That said, previous research on patients with psychotic and bipolar disorders indicates increased cortical thickness in the frontal and parietal cortices at baseline, correlating with enhanced cognitive improvements following CR (30, 31, 33, 34). Thus, we may tentatively hypothesize that increased cortical thickness in these regions will predict significant improvements in cognitive function after FROA-BD.

Finally, the study also hypothesizes that there may be potential differences depending on sex.

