### Sample size estimation

2.2

We aim to include 28 participants because previous studies with 23–28 participants found effects (29–31). In addition, with this sample size, we would have ~80% power to detect moderate correlations (r 0.56) after correcting for multiple testing (correlations in three ROIs: left dorsolateral, bilateral dorsomedial, and right dorsolateral prefrontal cortices). Note that this sample size does not include those patients who, even if consenting to participate, leave the study before finishing the baseline assessment and MRI acquisition.

As we anticipate the possibility of participant attrition during the follow-up, we plan to enroll 32 participants (i.e., ~15% more) to counteract the potential dropouts.

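### The exploratory sex analysis re-runs only pooled-significant results within each sex and states no comparison of the sexes, so it cannot show a difference and screens out the largest ones

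*Protocol article*

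**What the plan says.** Under Hypotheses, the article states that "the study also hypothesizes that there may be potential differences depending on sex". The method is given in Data analysis: "We will also repeat all the analyses on those results that reach statistical significance according to sex to explore potential differences". Objectives and the Discussion give the same rule. The abstract says "We will also conduct separate analyses by sex", and the Discussion also says that the exploratory analyses will be done separately, so the phrase about sex in Data analysis means two within-sex analyses.

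No section states an interaction term or a comparison of the male and female correlations. Sex otherwise enters the analysis only as one candidate covariate in the secondary analyses. A main-effect covariate does not address whether a correlation differs by sex.

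On numbers, Study design says "The sample will comprise at least 32 patients (50% males and 50% females"; Sample size estimation says "We aim to include 28 participants because previous studies" and "we plan to enroll 32 participants (i.e., ~15% more) to counteract the potential dropouts".

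**The concern.** The question is whether the link between brain change and functional change differs between men and women. That concerns the difference between two correlations. The plan produces two separate within-sex results, and only for findings that were already significant with the sexes combined.

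Two problems follow.

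- With about half the sample in each sex, a correlation that is the same in both will often reach significance in one and not the other by chance. Nothing in the stated method separates that pattern from a real difference.
- The pooled filter favours findings on which the sexes agree. If the correlations have opposite signs they cancel in the pooled sample, and the finding never reaches the sex analysis.

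At stake is the credibility of any sex-specific statement. The study recruits equal numbers of men and women and hopes to inform personalised treatment, so an apparent one-sex result could be carried further than it deserves.

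**Working it through.** **Inputs from the article.** 28 planned completers and 32 enrolled; a 50/50 sex split; a target correlation of 0.56 with about 80% power; three regions of interest corrected together.

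**Assumptions.** The overall level for the primary analysis is 0.05 two-sided, approximated as 0.05/3 = 0.0167 per region. Dropout is equal by sex, giving 28/2 = 14 per sex (32/2 = 16 if nobody drops out). Within-sex tests use two-sided 0.05. Data are bivariate normal, with equal means and variances in the two sexes.

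**Step 1: reproduce the plan's figure.** The plan claims about "80% power to detect moderate correlations (r 0.56) after correcting for multiple testing". By Fisher z, power = Φ(atanh(r)·√(n−3) − z), with atanh(0.56) = 0.633. For n = 28: 0.633 × √25 = 3.16; 3.16 − 2.39 = 0.77; Φ(0.77) = 0.78. Simulation with the t-test of r (200,000 runs) gives 0.79. The stated figure is reproduced.

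**Step 2: power within one sex.** For n = 14 at 0.05: 0.633 × √11 = 2.10; 2.10 − 1.96 = 0.14; Φ(0.14) = 0.56. Simulation gives 0.585. With 16 per sex, simulation gives 0.65.

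**Step 3: the plan's procedure against a direct test.** The direct test is (z_male − z_female)/√(2/(n−3)) at two-sided 0.05, where n is the number per sex. Simulation, 14 per sex, per region:

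| True r in the two sexes | Pass pooled screen | Of those, significant in exactly one sex | Direct test significant |
|---|---|---|---|
| 0.56 and 0.56 | 79% | 52% | 5% (false positives) |
| +0.56 and −0.56 | 3.3% | 94% | 87% |
| 0.56 and 0 | 18% | 87% | 34% |

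In the first row, 0.793 × 0.520 = 0.41, so 41% of all studies would show a one-sex pattern in a given region when nothing differs. With 16 per sex, 47% of screened results do so.

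**Step 4: analytic check of the direct test.** Standard error = √(2/11) = 0.426. Opposite signs: (2 × 0.633)/0.426 = 2.97; Φ(2.97 − 1.96) = 0.84. For 0.56 against 0: 0.633/0.426 = 1.48; Φ(1.48 − 1.96) = 0.32. Both are slightly below the simulated 87% and 34%.

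**Step 5: limit of the direct test.** The smallest difference detectable with 80% power and 14 per sex is (1.96 + 0.84) × 0.426 = 1.19 on the z scale: about +0.54 against −0.54, or 0.83 against 0.

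**The case against.** The strongest reply is that this is an exploratory look, labelled as such. The hypothesis says only that differences may exist, with no direction, size or power claimed, and the Discussion itself reports no clear sex effect on response to cognitive remediation. That stands, and it limits the severity. It does not make the method answer its question.

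Second, a reader might infer that the authors will take significance in one sex only as evidence of a difference. The article never says so. The percentages show what would happen if the results were read that way; they are not a prediction of how they will be read. How the two sets of estimates would be set side by side may be in an analysis plan that is not shown. The filter on pooled significance is stated outright, however, and would bind whatever comparison followed.

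Third, a reader might compute 2 × 0.585 × 0.415 = 0.49 and say that half of all studies would show a spurious sex pattern. That ignores the filter: the figure is 41% of studies per region, or 52% of results that pass. With no correlation in either sex, the filter holds the pattern to about 1% of studies per region. The filter therefore does protect against noise, and the problem arises where a real pooled effect exists.

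Fourth, a full sign reversal is an extreme example that nothing in the article suggests. That is fair. In the milder case of 0.56 against 0, the filter still removes about 82% (100 − 18), but a direct test would also usually miss it, with 34% power.

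**Conclusion.** The concern holds for the exploratory sex analysis. The stated rule cannot show whether correlations differ by sex, and it mostly removes the results in which they differ most. This is a mismatch between a stated hypothesis and a stated rule, not detail left to another document.

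The percentages rest on 14 completers per sex with equal dropout, a pooled level of 0.05/3 and an assumed within-sex level of 0.05. Moving to 16 per sex changes the 52% to 47% and leaves the conclusion as it is.

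The documents do not support a stronger claim. The primary correlations are analysed in the pooled sample and are unaffected. Opposite-sign effects are screened out in about 97% of cases at ±0.56 (100 − 3.3), not always. Severity is low to moderate.

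**What to change.** For the three primary regions, whatever the pooled result, estimate the difference between the male and female correlations with a 95% confidence interval, labelled exploratory. A sex-by-activation-change interaction would also serve. It compares slopes rather than correlations, so the two can diverge if variances differ by sex. It also needs a permutation scheme suited to interactions, such as permuting residuals; the scheme for a simple correlation does not carry over directly.

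For secondary results carried into the sex analysis, report the between-sex difference with a confidence interval, and note that selecting on pooled significance limits which differences can be seen. An interaction map for every modality and outcome is not needed: it would add much work and a further multiplicity problem.

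Give sex-specific correlations descriptively with confidence intervals, and state that significance in one sex only will not be read as a sex difference.

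The cost is a change of wording and slightly more analysis, with no new participants or scans. Power for modest differences stays low, and the interval will show that openly. The change should be made before results are seen, because the present filter depends on them.
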